### Randomization

The randomization will be done at the operational district level (cluster), the third tier of Cambodia’s health system. To address the issue of contamination that may arise and maintain comparability between the two arms (balanced randomization) at baseline, we performed a matched-pair selection of 10 provinces (five for each arm) out of the 25 provinces in Cambodia based on similar levels of MCH-SES index and NMCHC’s recommendations (Table 1). We used the principal component analysis approach [22] to construct the provinces’ MCH-SES index from a basket of indicators of ANC, delivery, and PNC from the Cambodia Demographic and Health Survey (CDHS) 2021 [4] and indicators of socioeconomic status from the National Population Census 2019 [23] and Cambodia Socioeconomic Survey 2019 (CSES) [24]. The indicators from CDHS 2021 included the proportion of pregnant women attending at least four ANC, the proportion of women delivering in a health facility, the proportion of women having a PNC visit in the first 2 days after delivery, the proportion of fully vaccinated (basic antigen) children aged 12–24 months, the proportion of fully vaccinated (according to the national schedule) among children aged 12–24 months, and proportion of children aged 12–24 months without vaccinations. The indicators from the population census 2019 included population density, literacy rate of the population aged 7 years and older, the proportion of the population aged 15 years and older with secondary education or higher, the proportion of households with electricity, and the proportion of households with piped water in a dwelling, while median monthly income per capita in thousand Khmer riels was from the CSES 2019.

**Table 1 Tab1:** List of matched-pair provinces with their respective MCH-SES indices

Pair	Matched province	MCH-SES index	Matched provinces	MCH-SES index
1	Kampong Speu	1.11	Kampong Chhnang	1.38
2	Pailin	0.37	Pursat	0.12
3	Kampot	− 0.17	Preah Sihanouk	0.15
4	Oddar Meanchey	− 1.07	Kampong Thom	− 1.34
5	Preah Vihear	− 2.75	Ratanak Kiri	− 7.77

*MCH* Maternal and child health, *SES* Socioeconomic survey

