As shown in Fig. 2, we will randomly select one operational district from each province after visiting study sites and excluding ODs in the provincial town (urban area) and those without Internet coverage. Within each pair of the 10 selected provinces, we will randomly assign one operational district to an intervention arm and the other to a control arm using Excel (Microsoft). Blinding to the participants, including HC staff, VHSGs, and the beneficiaries, would not be possible in this community-based intervention study. We also have no plan to make the allocation blind to the outcome assessors and data analysts. We will then randomly select two HCs from each operational district after excluding those covering less than 10 villages and without Internet coverage. In Cambodia, HCs provide a minimum package of activities, such as preventive and primary curative services, each serving approximately 10,000 to 20,000 people in villages under its coverage [25]. The number of HC staff may vary between eight and 11. The staff members typically include medical doctors (uncommon), midwives, nurses, and supporting staff.

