### Sample size

We used a sample size calculator for the cluster RCT and a practitioner’s guide to sample size and power calculation by McConnell and Vera-Hernandez [26] to estimate sample size and power for this study. Given the absence of similar studies in Cambodia, our assumptions were based on those used in a similar study in India with some adjustments. We assumed the intra-cluster correlation (ICC) to be 0.02 and the effect size of 13%, slightly below the 15% in India [18]. We observed that the MCH coverage index constructed from indicators of at least four ANC visits, PNC visits in the first 2 days after delivery, and complete immunization of children aged 12–24 months in 2021 in our selected provinces is at 70%, higher than the 36% of the MCH composite index in India [27]. Our cluster size was approximately 200, assuming there are two HCs per operational district, 10 villages per HC, and 10 mothers or pregnant women per village. The confidence level was set at 95%, while each arm consisted of five clusters. After obtaining a sample of 1858 mothers (929 per arm) and a power of 85%, we accounted for a 5% non-response rate and arrived at a sample size of 1951 mothers for both arms.

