### Analysis plan

#### Quantitative data

##### Data from household surveys, mobile applications, and web interface

We will use Stata 17 (StataCorp LLC, [name]) for quantitative data analyses. Since the randomization will be performed at the cluster level, all pregnant women and infants in the intervention arm will be eligible for the program. We will conduct intention-to-treat (ITT) analyses to examine the *i-MoMCARE*’s impact on outcomes of interest. Additional analyses will be per the study protocol analyses. We will analyze household data by considering cluster randomization design. The matched-pair method introduced in the earlier section is to achieve balanced randomization rather than representing a matched dataset when individual participants serve as their controls. Therefore, our analysis must consider this matching. We will test (i.e., Student’s *t*-test and chi-square test) the differences in the means or proportions of the maternal and child characteristics in the intervention and control arms at the beneficiary and cluster levels to observe balances in the study arms at baseline. In case of an imbalance in certain specific characteristics, we will apply a generalized estimating equation (GEE) approach to account for this imbalance. We will employ a difference-in-difference method using the GEE approach for all outcomes of mothers, pregnant women, and infants collected at baseline and endline. We will cluster standard errors at the village level to account for intra-cluster correlation in the characteristics of mothers. To account for multiplicity that may arise from testing multiple endpoints (i.e., primary and secondary outcomes) and lead to false rejection of the null hypothesis of no effect (type I error), we will apply the Bonferroni method and resampling-based method (i.e., bootstrapping) to obtain appropriate *p*-values [36].

To calculate children’s nutritional status, we will enter data on weight, height, sex, and date of birth into the Essential Nutrition Action software (ENA 2011) to compare the weight-for-age, height-for-age, and weight-for-height data to the international WHO reference standards. Data from the mobile phone application and web interface will be analyzed using a before-and-after method to determine the changes in the process indicators (Table 5).

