We will conduct a sensitivity analysis to ascertain the effect size in our analyses. The GEE method has recently been criticized for inflating the type 1 error, resulting primarily from the incorrect standard errors obtained from the GEE method when the number of clusters is small [37]. Since the number of clusters in our study will be 10 ODs (< 30 clusters), we will conduct further analyses using the finite-sample corrected GEE bias correction [38, 39] and covariate adjustment methods [40, 41] to obtain the correct standard errors and make appropriate inferential analyses.

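### The main difference-in-difference clusters standard errors at the village although operational districts are randomised; the small-sample method that counts 10 districts is only a sensitivity analysis

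*Protocol article*

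**What the plan says.** All of this is in the protocol article.

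- **Randomization:** "The randomization will be done at the operational district level (cluster"). Within each of the five matched pairs, "we will randomly assign one operational district to an intervention arm and the other to a control arm".
- **Sample size:** "The confidence level was set at 95%, while each arm consisted of five clusters". "We assumed the intra-cluster correlation (ICC) to be 0.02 and the effect size of 13"%. The cluster size is about 200: two health centres per OD, 10 villages per health centre and 10 women per village.
- **Analysis plan, household surveys:** outcomes measured at baseline and endline are analysed by GEE difference-in-difference, and "We will cluster standard errors at the village level to account for intra-cluster correlation in the characteristics of mothers". The same paragraph says that the cluster design will be taken into account and, of the pairs, "Therefore, our analysis must consider this matching".
- **Next paragraph, introduced as a sensitivity analysis:** "Since the number of clusters in our study will be 10 ODs (< 30 clusters"), further analyses will use a finite-sample corrected GEE and covariate adjustment to obtain correct standard errors.

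**The concern.** The plan uses two different clusters. For randomisation, sample size and the sensitivity analysis the cluster is the OD, of which there are 10. For the standard errors of the main analysis it is the village, of which there are about 200, roughly 20 nested in each OD.

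The difference-in-difference removes stable differences between ODs. It does not remove change specific to an OD between the two surveys, such as a new programme, a staffing change or a local outbreak during the 24-month intervention. Every village in the OD shares that change, and it is aligned with the arm because the whole OD is in one arm. Standard errors clustered at the village treat it as 20 independent pieces of information. The main p-values and confidence intervals could then present between-district drift as an intervention effect, while the method that the plan itself describes as giving correct standard errors sits in a subordinate analysis.

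**Working it through.** **1. Which cluster does the sample size use?** Inputs from the Sample size section: coverage 70% ("in our selected provinces is at 70%, higher than the 36% of the MCH composite index in India"), a difference of 13 percentage points (so 83%), 95% confidence taken as two-sided 5%, power 85%, ICC 0.02, cluster size 200.

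- Unpooled two-proportion formula: (1.960 + 1.036)² × (0.70×0.30 + 0.83×0.17) / 0.13² = 8.978 × 0.3511 / 0.0169 = 186.5 per arm.
- Design effect: 1 + (200 − 1) × 0.02 = 4.98.
- 186.5 × 4.98 = 929 per arm and 1858 in all; × 1.05 = 1951.

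This reproduces the stated figures exactly, so the trial was sized with the OD as the cluster.

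**2. Type I error of the main analysis.** Let ρ = 0.02 be the OD-level ICC and r the correlation of an OD's effect between baseline and endline. The document does not give r, so it is varied. Assume 20 villages of 10 different mothers per OD in each survey and no extra village-level correlation. Apart from a common factor that cancels:

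- true variance: ρ(1 − r) + (1 − ρ)/200
- variance estimated with village clustering: ρ(1 − r)/20 + (1 − ρ)/200
- type I error: 2 × [1 − Φ(1.96 / √ratio)]

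| r | true | estimated | variance ratio | SE ratio | type I error |
|---|---|---|---|---|---|
| 0 | 0.0249 | 0.0059 | 4.22 | 2.05 | 34% |
| 0.5 | 0.0149 | 0.0054 | 2.76 | 1.66 | 24% |
| 0.8 | 0.0089 | 0.0051 | 1.75 | 1.32 | 14% |
| 0.9 | 0.0069 | 0.0050 | 1.38 | 1.17 | 9.5% |
| 0.95 | 0.0059 | 0.00495 | 1.19 | 1.09 | 7% |
| 1 | 0.0049 | 0.0049 | 1.00 | 1.00 | 5% |

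Simulation (10,000 runs per setting) gave 35%, 25%, 14%, 9.5% and 5% at r = 0, 0.5, 0.8, 0.9 and 1.

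**3. Sensitivity to the inputs, for r from 0.9 down to 0.**

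- If the 1951 covers both survey rounds together, about 100 women per OD and round, replace 200 by 100 in the formulas: 7% to 24%.
- OD ICC 0.01: 7% to 24%. OD ICC 0.05: 16% to 48%.
- Adding a village ICC of 0.03 at OD ICC 0.02: 9% to 32%.

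**4. Does OD-level inference repair it?** In the same simulations a t-test on the 10 OD-level changes (8 df) held 4.6% to 5.4%. OD-clustered robust standard errors with no small-sample correction and a 1.96 cut-off rejected in about 12% of runs. The OD level and the small-sample correction are therefore both needed.

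**5. Power under a t reference.** From the plan's inputs, the standard error is √(0.3511 × 4.98 / 929) = 0.0434 and the noncentrality is 0.13 / 0.0434 = 3.00. With a normal reference, Φ(3.00 − 1.96) gives the stated 85%. With a noncentral t, power is about 75% at 8 df (critical value 2.31) and 62% at 4 df (critical value 2.78), before any variance reduction from pairing or baseline data.

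**The case against.** The strongest reply is that the plan already knows the answer: its next paragraph counts 10 ODs, names the small-cluster type I error problem and commits to a corrected GEE. That stands in part. The right method is planned, and it would be unfair to say that the trial has no valid analysis. But it is labelled a sensitivity or further analysis, and nothing there replaces the village rule. The small-cluster worry would also make no sense with about 200 village clusters, so the two paragraphs contradict each other. Nor is this detail left for an SAP, since the protocol states the level explicitly.

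A second reply is that the difference-in-difference cancels district effects. This is true for stable effects, and it limits the size of the problem. A reader might infer that false positives will run at 10% to 35%. The documents do not support this as a finding: it is the result of assuming r between about 0.9 and 0. Inflation is about 7% at 0.95 and nil at 1. A twofold understatement of the standard error, √(4.98/1.18) = 2.05, likewise describes a single-survey comparison or the r = 0 extreme, not the planned analysis in general.

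The planned Bonferroni and bootstrap adjustments do not settle the matter. The rates above are per test before adjustment, Bonferroni cannot repair a wrong standard error, and the resampling unit of the bootstrap is not stated.

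Two further criticisms are tempting and are not made here. The absence of a written pair term is model detail that an SAP can supply, given the stated commitment to consider the matching. The composite index combines proportions with different denominators, but clustering standard errors by village does not require an index value for each village.

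**Conclusion.** The main-analysis rule is wrong as written and must be changed. It sets the clustering of the standard errors below the unit of randomisation, and it conflicts with the sample size and with the plan's own sensitivity paragraph. The direction of the error is certain if districts change differently over time; its size is conditional. At the plan's ICC of 0.02, type I error lies anywhere from 5% to about 34%, depending on a baseline–endline correlation that would have to be close to 1 for the error to be negligible. These figures assume about 200 women per OD in each round, use the plan's ICC at the OD level and ignore the matching. Matching can reduce the OD-level variance, but it does not make the villages within an OD independent.

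**What to change.** Replace village-level clustering in the primary analysis with inference at the OD level. Choose one of these before outcome data are seen:

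- GEE clustered on the OD, with the finite-sample correction that the sensitivity paragraph already names. Add a t reference distribution, which that paragraph does not mention.
- A comparison of OD-level changes from baseline to endline that reflects the pairs. The t reference has 4 df if paired and 8 if unpaired, or one fewer (3 or 7) if baseline is fitted as a covariate instead of being subtracted.

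Village clustering may stay only as a labelled secondary analysis. If the bootstrap is kept for multiplicity, say that whole ODs are the resampling unit.

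The edit is to protocol and SAP wording, but it has a price. Confidence intervals widen, and the stated 85% power no longer holds on the plan's inputs, so power should be restated for the chosen analysis. The paired option preserves the design but has the fewest degrees of freedom, so whether pairing gains enough variance to pay for them should be weighed when choosing.

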**Methods:**

i-MoMCARE, a two-arm cluster randomized controlled trial, will be conducted between 2022 and 2025. Five operational districts (ODs) have been randomized to an intervention arm and the other five ODs to the control arm. The intervention will last for 24 months. Around 200 VHSGs in the intervention arm will be equipped with a mobile application as a job aid and 20 HC staff with a web interface to improve support and supervision of VHSGs. The potential beneficiaries will include pregnant women, mothers, and children under 2 years old. We will measure the outcomes at baseline and endline. The primary outcomes will consist of a composite MCH index constructed from maternal and newborn care indicators, child immunization, and treatment of under-two children. Secondary outcomes will include coverage of selected MCH services. We will conduct the intention-to-treat and per-protocol analyses. We will conduct qualitative interviews with selected beneficiaries and stakeholders to evaluate the intervention’s acceptability, feasibility, and scalability. We will also conduct a cost-effective analysis using decision-analytic modeling incorporating a societal perspective that explores different time horizons, intervention effects, and when scaled up to the national level.

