#### Primary outcomes

VHSGs will facilitate the primary outcomes of interest throughout the continuum of care, including (1) the proportion of neonates/mothers visited at home by VHSGs at least twice within the first week of delivery, (2) the proportion of mothers receiving information from VHSGs regarding danger signs of newborn illnesses within the first week of delivery, and (3) the MNCH composite coverage index, consisting of four dimensions, namely maternal care, neonatal care, infant care, young childcare, and care-seeking when having complications.

The MCH composite index was initially introduced by Boerma et al. [31, 32]. It captures a complete continuum of care of mothers and children by including four dimensions: family planning, maternal and newborn care, immunization, and treatment of children. Following Modi et al. [27], we will exclude family planning to focus more on the role of the VHSGs in evaluating the effectiveness of mobile health technology. The three components will be equally weighted. The index will be calculated using the following formula: MCH-CI = 1/3 (¼ APNC + ½ IMMU + 1/3 TREAT), where APNC denotes antenatal and postnatal care, IMMU denotes immunization among children, and TREAT denotes the treatment of children. The index will vary between 0 and 100, with a higher index score indicating a higher MCH coverage. We will use the MCH coverage index to evaluate the effectiveness of the intervention. We have conjectured that the coverage rate should be well above 60% to be meaningful since earlier estimates of the compelling national coverage of maternal health services (ANC and facility delivery) and sick childcare (diarrhea, pneumonia, and fever) in 2014 were 56.4% and 59.1%, respectively [33]. Another recent study using a slightly deviated measure of the mother and infant care continuum shows that the national coverage was 49.4% [34].

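### Bonferroni is described over primary and secondary outcomes together, while the 85% power was planned at alpha 0.05 with no allowance for multiplicity

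*Protocol article*

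**What the plan says.** **Multiplicity.** The analysis plan for household survey data says: "To account for multiplicity that may arise from testing multiple endpoints (i.e., primary and secondary outcomes"). It then promises Bonferroni and a resampling method (bootstrapping) to obtain p-values. It gives no divisor, no separate primary family and no order of testing.

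**Primary outcomes.** The Primary outcomes section introduces a list: "VHSGs will facilitate the primary outcomes of interest throughout the continuum of care, including (1"). The list has three entries: at least two home visits by village health support groups (VHSGs) in the first week, danger-sign information from VHSGs in the first week, and the composite coverage index. The abstract mentions only the index: "The primary outcomes will consist of a composite MCH index constructed from maternal and newborn care indicators".

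**Secondary outcomes.** Table 5 lists 28 maternal and child items plus five process indicators. The process indicators are to be analysed before-and-after.

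**Planning alpha.** The Sample size section says: "The confidence level was set at 95%, while each arm consisted of five clusters". The other inputs are "We assumed the intra-cluster correlation (ICC) to be 0.02 and the effect size of 13"%, a coverage index that "in 2021 in our selected provinces is at 70%, higher than the 36% of the MCH composite index in India", and "Our cluster size was approximately 200". The result is 929 mothers per arm at 85% power. Nothing is set aside for more than one test.

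**The concern.** The sample size and the analysis plan use different significance levels. If the index is tested at 0.05 divided by the number of primary and secondary outcomes, the trial does not have its stated 85% power for it. The main question then pays for dozens of supporting ones. A true effect of the size planned for could be declared not significant because of how the outcomes were grouped. Even if only the three primary outcomes share alpha, the power statement no longer matches the test.

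**Working it through.** **1. Reproduce the plan's figure.** Inputs from Sample size: 70% in control, 13 points of effect (so 83%), ICC 0.02, cluster size 200, 95% confidence, 85% power. Two-sided testing is assumed, since sidedness is not stated.

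- Variance: 0.70 × 0.30 + 0.83 × 0.17 = 0.3511
- Unclustered n per arm: (1.960 + 1.036)² × 0.3511 / 0.13² = 186.5
- Design effect: 1 + 199 × 0.02 = 4.98
- n per arm: 186.5 × 4.98 = 929. This matches the protocol exactly, so the 85% is a normal-approximation power at an undivided 0.05.

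**2. Count the family.** Table 5: ANC 4 + delivery 5 + PNC 4 + neonatal 5 + young infant 6 + young child 4 = 28. Adding the three primary outcomes gives 31. The five process indicators are left out because they are not two-arm comparisons. The count is a minimum, because several lines hold more than one endpoint (for example stunting, wasting and underweight).

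- 0.05/31 = 0.00161
- 0.05/3 = 0.01667

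**3. Noncentrality.** This is 0.13 / √(0.3511 × design effect / 929).

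- Design effect 4.98: standard error 0.0434, noncentrality 3.00
- Design effect at the actual 929/5 = 185.8 per cluster, 1 + 184.8 × 0.02 = 4.696: standard error 0.0421, noncentrality 3.09

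The ranges below span these two values.

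**4. Power on the plan's own basis (normal approximation).** Power = Φ(noncentrality − critical value).

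| Alpha | Critical z | Power |
|---|---|---|
| 0.05 | 1.96 | 85–87% |
| 0.05/3 | 2.39 | 73–76% |
| 0.05/31 | 3.15 | 44–47% |

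**5. Separate question: a t reference on the randomised ODs.** Ten ODs give 8 degrees of freedom unmatched; five pairs give 4. Power is from the noncentral t distribution with the same noncentrality.

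| Alpha | Critical t, 8 df | Power, 8 df | Critical t, 4 df | Power, 4 df |
|---|---|---|---|---|
| 0.05 | 2.31 | 75–77% | 2.78 | 62–64% |
| 0.05/3 | 3.02 | 53–56% | 3.96 | 34–37% |
| 0.05/31 | 4.67 | 16–17% | 7.59 | 6% |

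The first row shows what few clusters cost on their own, before any correction for multiplicity. The rows below add the division of alpha.

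**The case against.** **One family is an inference.** The parenthesis says where multiplicity comes from. It states no divisor and does not rule out separate families, and a statistical analysis plan that is not shown may settle this. That is fair, and 31 is therefore a reading, though the natural one: the sentence names both tiers together and separates them nowhere. The mismatch with the sample size does not depend on it, because three primary outcomes sharing 0.05 already lower the planned power.

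**The most tempting overstatement.** A reader might infer that Bonferroni alone cuts power to 6–17% and that the primary analysis is nearly certain to fail. The document does not support that. Those figures need an OD-level t reference with 8 or 4 degrees of freedom, which the plan does not specify. The main model clusters standard errors at village level, the finite-sample corrections appear as further sensitivity analyses, and the matching is only said to need consideration.

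**The planning model is not the planned analysis.** The analysis is a difference-in-difference GEE, whereas the calculation compares two proportions at one time. The 70% comes from a three-indicator index, while the primary index has nine sub-components. Both points stand and limit the figures to the planning model.

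**The bootstrap.** A resampling method that uses the correlation between outcomes would lose less power than Bonferroni. This stands. The absence of a rule on which adjusted p-value decides is largely detail that an analysis plan would supply.

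**The two VHSG-contact outcomes.** A reader might infer that they do not belong among the primary outcomes because they measure delivery of the intervention. The protocol justifies them from a formative study, and four of the index's nine sub-components also measure VHSG visits or care. Demoting them on that ground would be a preference, not the correction of an error.

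**Conclusion.** The concern holds in a limited form. The stated 85% power applies to one test at two-sided 0.05, while the analysis plan describes adjustment across primary and secondary outcomes. On the protocol's own planning basis, Bonferroni over 31 tests roughly halves the power, to 44–47%; over the three primary outcomes it is 73–76%. The lower values in step 5 combine this with the separate cost of having ten clusters and are conditional on an analysis that the protocol does not fix.

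All figures assume 70% vs 83%, ICC 0.02, a two-sided test and a single-time comparison. The variance of the difference-in-difference estimate and of the nine-component index cannot be derived from the document. The abstract and Methods also disagree on whether there is one primary outcome or three, which determines the alpha that power should be stated for.

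**What to change.** - Limit familywise alpha control to the primary outcomes: either Holm over the three listed in the Primary outcomes section, or the composite index alone at two-sided 0.05 if it is the single primary outcome, as the abstract suggests. Reconcile the abstract and Methods accordingly.
- Treat secondary outcomes as a separate, supportive family (Holm or false discovery rate) that takes no alpha from the primary.
- Name one adjustment as decisive; any other is then a sensitivity analysis.
- Restate the power at the alpha actually used.

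This is a change of wording and a short recalculation, with no new data and no change to recruitment. The costs are that secondary outcomes carry supportive weight only, and that the stated power becomes less favourable if three primary outcomes are kept.

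### Bootstrapping is named for the multiplicity-adjusted p-values but not tied to ten districts randomised in five pairs; done in the ordinary way it would not hold the 5% family-wise error

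*Protocol article*

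**What the plan says.** The quantitative part of the Analysis plan treats multiplicity as the risk from "testing multiple endpoints (i.e., primary and secondary outcomes" and answers it with: "we will apply the Bonferroni method and resampling-based method (i.e., bootstrapping) to obtain appropriate *p*-values". In the same paragraph, standard errors are clustered at the village, and the analysis is said to have to take the matching into account. No resampling unit is given for the bootstrap.

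The design is in the Randomization section: "Within each pair of the 10 selected provinces, we will randomly assign one operational district to an intervention arm"; its partner in the pair serves as control. There are therefore five randomised pairs. The Sample size section adds: "The confidence level was set at 95%, while each arm consisted of five clusters".

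The sensitivity-analysis paragraph recognises the small number of clusters: "Since the number of clusters in our study will be 10 ODs (< 30 clusters), we will conduct further analyses using the finite-sample corrected GEE". Covariate adjustment is named alongside it. The stated aim is to correct the GEE standard errors. The paragraph does not mention the bootstrap.

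**The concern.** The multiplicity step exists to limit false claims. A bootstrap can do this only if its resamples reproduce the variation that matters for a randomised comparison, which here is variation between ODs. With five pairs, or five ODs per arm, an ordinary bootstrap falls short in two ways. Its variance is 4/5 of the unbiased estimate, and its reference distribution has near-normal tails where t tails on about 4 to 8 df are needed.

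The protocol accepts that ten ODs are too few for ordinary GEE inference. It does not carry that to the bootstrap, where the cause is the same. Moving the clustering from villages to ODs would not cure it either. If p-values from an ordinary bootstrap supported the trial's claims, a positive result on one of the three primary outcomes could be a false positive several times more often than the nominal 5%.

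**Working it through.** **Inputs from the protocol.** Ten ODs, five per arm, in five pairs; three primary outcomes; 95% confidence (two-sided 5% assumed); ICC 0.02; baseline 70%; effect 13 points; about 200 mothers per OD; about 10 per village.

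**The plan's own figure.** The protocol states no error rate for the bootstrap, so its sample size is used to confirm the inputs. For 0.70 against 0.83: (1.960 + 1.036)² × (0.21 + 0.1411) / 0.13² = 8.978 × 0.3511 / 0.0169 = 186.5 per arm. The design effect is 1 + 199 × 0.02 = 4.98, and 186.5 × 4.98 ≈ 929 per arm, as stated.

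**Why few clusters matter.** For five pair differences with sample variance s² (divisor 4), the bootstrap variance of the mean is (4/5) × s²/5. A test using the bootstrap SE and a normal quantile z therefore rejects when |t| > z × √0.8.

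- Pairs, 4 df, one outcome: threshold 1.960 × 0.894 = 1.753, so P = 15.4%.
- Pairs, Bonferroni for three: threshold 2.394 × 0.894 = 2.141, so P = 9.9% each. For three independent outcomes, 1 − (1 − 0.099)³ = 26.8%.
- ODs within arm, no pair effect, 8 df: 11.8% for one outcome and 6.5% each after Bonferroni. Family-wise, 1 − (1 − 0.0647)³ = 18.2%.

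**Simulation under no effect.** OD-level normal summaries, 999 resamples, 2,000 trials per setting, three outcomes. Two quantities the protocol does not give were assumed: outcome correlation 0 to 0.8, and pair-effect SD of 0 to 1 times the within-pair OD SD.

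| Method, nominal 5% | Family-wise error |
|---|---|
| Pairs, percentile + Bonferroni | 22–32% |
| Pairs, centred unstudentised max statistic | 22–30% |
| Pairs, bootstrap SE + Bonferroni | 18–27% |
| ODs within arm, ordinary, no pair effect | 18–20% |
| ODs within arm, ordinary, pair SD 0.5 | 8–10% |
| ODs within arm, ordinary, pair SD 1 | 4–5% |
| Studentised, null-centred (pairs or ODs) | 0.4–1.7% |
| Pooled-residual Westfall–Young, studentised | 1.2–6.0% |
| Bonferroni on paired t, 4 df | 3.8–5.3% |

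With 30 outcomes (correlation 0.3, no pair effect; 600 trials), close to the 3 primary plus 28 non-process outcomes in Table 5, ordinary versions reach 44–84% and Bonferroni on the paired t gives 5.8%.

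**Under the planned difference-in-difference.** Assumptions: outcome correlation 0.35, ICC 0.02, about 186 mothers per OD per survey, baseline–endline OD correlation 0.5–0.8, pair share of OD variance 0 or 0.5. The pair bootstrap gives 28–31%, ODs within arm 10–19%, Bonferroni on OD-bootstrap SEs 9–17%, and Bonferroni on the paired t 4.3–4.8%. Cancellation of stable OD differences does not remove the problem.

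**Villages as the resampling unit.** In a cross-sectional comparison at ICC 0.02 with no extra village correlation, the village design effect is 1 + 9 × 0.02 = 1.18. The SE is too small by √(4.98/1.18) = 2.05. One outcome then rejects 34% of the time, and three independent outcomes with Bonferroni give 57%. At ICC 0.005 the latter is 23%. Under the difference-in-difference assumptions above it is 12–36%.

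**Other candidates.** Within-pair permutation has a smallest two-sided p of 2/2⁵ = 0.0625, so it can never reach 5%. A null-imposed wild cluster bootstrap-t on ODs with pair fixed effects rejects about 13% for a single outcome and about 25% family-wise. Ignoring the pairs, it rejects 1.6–5.2% for a single outcome.

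**The case against.** The strongest reply is that the protocol does not specify the method being criticised. It gives no unit, null or studentisation, the article is condensed, and an analysis plan not shown may name a sound variant. Studentised and pooled-residual bootstraps hold the error near or below 5%, and they too are bootstraps. This stands, and it makes every rate above conditional.

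A reader might infer that the trial's adjusted p-values will come from bootstrapping alone and will carry an error of 8–29%. The text does not support that. Bonferroni is named alongside, how the two combine is not stated, and ordinary OD resampling falls to 4–5% under strong pairing. Nor is failure to impose the null the main cause: centring without studentising still gives 22–30% when pairs are resampled. The village is named for the GEE standard errors, not for the bootstrap, so the village figures show only what would follow if that unit were carried over.

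What the reply does not remove is that the protocol makes a positive choice of method. Unqualified, that choice covers procedures with error from under 1% to about 30%. Strong pairing helps only a scheme that ignores the matching the plan says it must consider; ordinary resampling of pairs, which respects it, gives the highest rates among the whole-OD schemes.

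**Conclusion.** The point holds in conditional form. An ordinary bootstrap of this design would give a family-wise error for three outcomes of about 22–32% when pairs are resampled (18–27% in the bootstrap-SE version) and about 4–20% when ODs are resampled within arm. It would be above nominal when villages are resampled. Bonferroni on top does not help, because the p-values it multiplies are already too small. Studentising reverses the error to about 0.4–2%, at the expense of power. The sensitivity analysis described for GEE standard errors does not, as written, extend to these p-values.

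The sizes rest on normal OD summaries and on assumed outcome correlation and pair strength. The direction for pair resampling follows from the 4/5 variance factor and the 4 df alone. Because a method with about the right error is available at no data cost, this is more than a request for detail.

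**What to change.** In the quantitative Analysis plan, replace the bootstrapping clause. State that multiplicity-adjusted p-values are obtained by Bonferroni or Holm applied to small-sample OD-level p-values that respect the pairs, namely a paired t-test on OD summaries of the baseline-to-endline change with 4 df. State also that claims are not based on ordinary bootstrapping of mothers, villages, ODs or pairs. Family-wise error is then about 4–5% (Bonferroni 3.8–5.3%, Holm 4.2–4.8%).

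Neither a wild cluster bootstrap-t with pair fixed effects nor within-pair permutation should be offered as the alternative, for the reasons shown in the working.

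The cost is one sentence and a different command, with no new data. The downside is larger p-values and less apparent power: the Bonferroni threshold for three outcomes rises from 2.39 on the normal scale to 3.96 on t with 4 df.
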